#### 8.2.4. Data Types and Data Analysis

Phase 1. Qualitative data will be collected from focus group interviews and cognitive interviews, which will be transcribed verbatim. Phase 2. Two more sets of qualitative data will be collected from the stakeholders and moderators via interviews. Phase 3. Five measurements will be made: baseline, after the 8-week intervention (Month 2), after the 1st booster session (Month 3), after the 2nd booster session (Month 4) and after the last (3rd) booster session (Month 6). Primary outcome: eHealth Literacy Efficacy, measured by the eHealth Literacy scale (eHEAL), an 8-item self-reported efficacy scale scored on a 5-point Likert scale [14]. Secondary outcomes: Digital Health Literacy Instrument (DHLI) [44] and vaccine literacy (which includes intention to receive the COVID-19 vaccine) [38]. Knowledge and health behaviours related to COVID-19 prevention and the participants’ engagement in all activities will be assessed via Facebook Insights. Knowledge will be measured by 12 true-or-false items with a total score ranging from 0 to 12; attitudes towards COVID-19 will be measured by 2 yes-or-no items with a total score ranging from 0–2, and self-protection behaviours will be measured by 3 yes-or-no items with a total score ranging from 0 to 3. The self-protection behaviours are self-reported in three items: (1) going to crowded places, (2) whether wearing face masks when outside their home during the week before taking the survey, (3) whether washing their hands for 20 s each time when they return home or are in contact with another person) in yes-or-no answer [45,46]. Participants can report their behaviours and other outcomes in a link (that leads to an online survey in Qualtrics) in the Facebook.

Data analysis. Phases 1 and 2. The qualitative data analysis will occur in two steps. In the first step, a researcher will read through the transcripts and develop a codebook with definitions. Another researcher will then review the transcripts and add emergent codes as appropriate. The codebook and the definitions will be refined via discussion between the academic researchers and stakeholders. The second step of the analysis will focus mainly on the identification of themes and subthemes and on obtaining consensus across the team. Phase 3. To examine between-group differences in changes in the outcomes, we will perform separate linear mixed-effects models for each of the continuous outcomes (eHEAL, DHLI, vaccine literacy, knowledge, attitudes, and practices towards COVID-19) and three independent variables: ‘Time’, ‘Group’ and their interaction term ‘Time × Group’. A significant result of the interaction term (Time × Group) will indicate a differential change in the outcome variable between the two groups.

## 9. Study 3

#StayOkayHK: A universal public health initiative to promote stay-at-home during COVID-19

This project will develop and test a novel universal public health initiative (#StayOkayHK), incorporating a public health communication campaign, health education and promotion, and participatory social media strategies to encourage the HK public to stay at home to reduce the risk of SARS-CoV-2 transmission.

Participatory social media approach as a novel strategy to engage the HK public. It is estimated that 83% of HK citizens participate in social media and they spend an average of 13 h per week on these platforms [47]. Therefore, social media-based public health campaigns can be an effective strategy to engage citizens across sociodemographic groups. Further, the medium-long-term management of the pandemic and the changes it imposes on social norms and life rules call for additional strategies that empower the community to practice safe behaviours collectively and proactively. Therefore, we argue that adopting a participatory approach to engage the public in the content creation process and exchanging user-generated content will confer additional impact on the dissemination, uptake, and maintenance of COVID-19 public health campaigns. Indeed, research shows that user-generated content (e.g., videos and comments) enhances social identification, self-efficacy in performing health-promoting behaviours, and source credibility of information in health campaigns [48]. Moreover, it cultivates a positive affect and provides opportunities for creative self-expression in health-promotion initiatives [49]. Although no such public health campaign has been implemented in HK, evidence suggests that HK citizens have high levels of trust and willingness to peruse and share experienced-based health information on social media platforms [50,51].

Theoretical framework. This proposed public health initiative (#StayOkayHK) will be developed in accordance with Protection Motivation Theory (PMT) [52], which posits that environmental or intrapersonal sources of information about a health threat, such as communication campaigns, verbal persuasions, and the media, initiate the following two cognitive processes: (1) threat appraisal, comprising perceived vulnerability to and severity of the health threat and (2) coping appraisal, comprising perceived self-efficacy and response efficacy of health-protective behaviour. The threat and coping appraisals combine to exert a positive influence on an individual’s protection motivation (i.e., their motivation and intention to engage in health-protective behaviours), and these relationships are further counterbalanced by the costs to engage in health-protective behaviours and the rewards from engaging in health-compromising behaviours. PMT was selected given its (a) specificity to the context of the present investigation on health communication and information exchange to motivate health-protective behaviours for a specific health threat; (b) parsimony in guiding the design and practical implementation of a small set of core intervention components with high predictive value, and (c) strong evidence base when applied in the context of compliance with COVID-19 risk-reduction strategies [53,54]. Thus, the present project does not aim to test the principles of PMT, but rather, to directly apply its core tenets to this proposed initiative.

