#### 8.2.1. Subjects

Phase 1. Thirty EM adults, 30 PWCI and 30 CGs will be recruited for focus group interviews before the development of the interventions begins. Another 10 EM adults (2 from each ethnic group), 10 PWCI and 10 CGs will be invited to participate in cognitive interviews. Phase 2. Twenty EM adults, 20 PWCI, 20 CGs and 6 moderators will be invited to participate. Phase 3. One hundred fifty-six EM adults, 156 PWCI and 156 CGs will be randomised to the intervention or the control group.

We estimated the sample size for the trial of each proposed study based on a previous eHealth Literacy study that reported a small-to-moderate effect size (d = 0.245) [38]. For the proposed study, with five repeated measurements over a 6-month period, a total sample size of 108 subjects (i.e., 54 per group) is required to achieve a power of 90% when using a repeated-measures analysis of variance to detect a significant between-group interaction effect at 5% significance (G*Power 3.1). Furthermore, assuming an attrition rate of 30% [39], 156 subjects (78 per group) will be recruited for each study.

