#### 8.2.3. Study Design

Phase 1. Each qualitative study will include three to five focus group interviews and five cognitive interviews. In the focus group interviews, the stakeholders will be encouraged to indicate their problems and concerns about DHL, propose resources/solutions and formulate a plan. Version 1 of the interventions will be based on these comments. Cognitive interviews will be conducted with the stakeholders when the version 1 interventions are available. Here, we will ask the stakeholders to go through the interventions step-by-step to evaluate their flow and content.

Phase 2. A feasibility and acceptability study with individual interviews will be conducted to collect views from 20 stakeholders and two moderators. The moderators will be the trained workers who facilitate online group discussions on social media platforms.

Phase 3. This will be a two-arm, prospective, parallel-group (1:1), randomised controlled trial.

Settings. Participants will be recruited from non-governmental organisations that provide services to EMs, PWCI and CGs.

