Interventions. ‘Self-determination Theory’ will be used to guide the development of the intervention. That is, we address ‘autonomy, competence and connection (or relatedness)’ when we develop the intervention. While we are inviting the stakeholders (EM, PWCI, CG) to co-create the intervention with us, we ascertain they feel in control of their own behaviours and goals (whether they are determined to do the best to prevent COVID-19). We will also support them to gain mastery of tasks and learn different skills. Additionally, we will make sure the stakeholders experience a sense of belonging (attachment) to the materials we develop. The interventions will be developed based on the Best Practices for Digital Health Literacy [40], WHO health literacy toolkits [41] and the findings of the interviews in Phase 1. The content to be covered in the intervention will include news about vaccines; alerts about COVID-19 preventive measures; guidelines on social distancing, COVID-19 screening test arrangements, vaccination and compulsory quarantines; COVID-19–related law enforcement; and self-monitoring of COVID-19 symptoms. The interventions will be designed for three social media and communication platforms (a closed Facebook Social Learning Group, YouTube and Viber/ WhatsApp). Facebook and YouTube were chosen because they are the top two social media platforms in HK (used by 82% and 81% of users in HK, respectively) [42]. The ‘Social Learning Group’ in Facebook is a closed system that protects participants’ privacy, and it serves as the key platform for learning the short-clip videos our group developed for a different study [43], including step-by-step instructions from the moderators, eight online exercises and eight interactive sessions. The videos will be co-developed with representatives of the respective ethnic groups in six languages (English, Indonesian, Hindi, Nepali, Urdu and Cantonese), uploaded to YouTube and shared in the Facebook Social Learning Group. Development of the intervention will also consider the latest situation of COVID-19 regarding the content and the mode of delivery of preventive measures and vaccination recommendations. PWCI and CGs require different types of health information; for example, PWCI need information about the contraindications of vaccination to the long-term drugs they are taking, whilst CGs need information about the latest policies regarding visit restrictions or vaccination arrangements for residential care homes. Both groups will be invited to participate in the development of the intervention.

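### Study 2 routes self-reported outcomes through Facebook, the platform that carries its intervention, names Facebook Insights as a source for knowledge and behaviour, and states no survey route for controls

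*Protocol article*

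**What the plan says.** Phase 3 of Study 2 is run separately in three populations. Section 8.2.3 gives the design: "This will be a two-arm, prospective, parallel-group (1:1), randomised controlled trial". The same section describes delivery over three platforms: a closed Facebook group, YouTube, and Viber or WhatsApp. Of the Facebook group it says that "it serves as the key platform for learning the short-clip videos".

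Section 8.2.4 sets five measurement times and names eHEAL as the primary outcome. On data sources it makes two statements:

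- One sentence has knowledge, health behaviours and engagement together as its subject, and ends: "engagement in all activities will be assessed via Facebook Insights".
- The reporting route is: "Participants can report their behaviours and other outcomes in a link (that leads to an online survey in Qualtrics) in the Facebook".

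Knowledge is a score from 12 true/false items. For behaviour, "self-protection behaviours will be measured by 3 yes-or-no items with a total score ranging from 0 to 3". The first two items are listed as "1) going to crowded places, (2) whether wearing face masks when outside their home", and the third is hand washing. Section 8.2.4 then analyses these scores, including practices, in linear mixed models with a Time × Group term.

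The control group is named in Sections 8.2.1 and 8.2.3. The article does not say what controls receive, whether they have any Facebook space, or how the survey reaches them.

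**The concern.** Two features of the stated method work against a randomised comparison.

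First, the named source does not fit the measure. Facebook Insights reports use of a page or group. It does not produce answers to true/false or yes/no questions. Taken as written, the data source for knowledge and behaviours conflicts with the items defined in the same section.

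Second, the only stated reporting route runs through the platform that carries the intervention. A participant who stops using the learning group also stops meeting the survey link, so response depends on engagement. Response may also depend on arm, because no route is given for controls. Outcome collection should not depend on use of the treatment under test. Answers not collected on time from disengaged participants or controls cannot be recovered at the analysis stage.

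A smaller matter is the 0–3 behaviour score. It adds one risk behaviour to two protective ones without stating a coding direction. It is the listed measure of preventive behaviour for the second objective in Section 8.1.

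**Working it through.** **1. The passages side by side (Study 2)**

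- Facebook space described: one, the closed learning group (8.2.3, Interventions).
- Role of that space: main learning platform. Its backend records are also used to assess fidelity (8.2.3, Procedures).
- Route for behaviours and other outcomes: a Qualtrics link on Facebook (8.2.4).
- Route for controls: none stated.
- Source named for knowledge and behaviours: Facebook Insights (8.2.4), against 12 true/false and 3 yes/no self-report items in the same section.

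Elsewhere the article does give this detail. Section 9.2.2 (Study 3) sends survey invitations by social media account, phone or email, with up to five attempts. Section 7.2.2 (Study 1) states parallel assessment of controls.

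**2. The plan's own sample size**

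Section 8.2.1 uses "a small-to-moderate effect size (d = 0.245") and states that "a total sample size of 108 subjects (i.e., 54 per group) is required to achieve a power of 90" per cent. Inputs: f = d/2 = 0.1225, m = 5 measurements, two groups, α = 0.05. The within-person correlation ρ is not stated, so 0.5 is assumed, with sphericity.

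Noncentral F for the within–between interaction: λ = N·f²·m/(1 − ρ), df1 = 4, df2 = 4(N − 2).

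- N = 108, f = 0.1225: λ = 108 × 0.01500625 × 5/0.5 = 16.21, df2 = 424, power 91.2%.
- N = 108, f rounded to 0.12: λ = 108 × 0.0144 × 5/0.5 = 15.55, power 89.9%.
- Attrition: 54/(1 − 0.30) = 77.1, so 78 per group and 156 in total, as stated.

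The result depends on ρ. At f = 0.1225, N = 108 gives 78.1% power for ρ = 0.3 and 99.3% for ρ = 0.7. The plan's figure is reproduced at ρ = 0.5, and the sample size is not in dispute.

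**3. Loss of precision if controls respond less (illustration)**

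Assume 70% response in the intervention arm: 78 × 0.70 = 54.6. Effective n per arm is the harmonic mean, 2/(1/n₁ + 1/n₀), with f = 0.1225 and ρ = 0.5.

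| Control response | n₀ | Effective n per arm | Power |
|---|---|---|---|
| 70% | 54.6 | 54.6 | 91.6% |
| 50% | 39.0 | 45.5 | 85.2% |
| 30% | 23.4 | 32.8 | 69.8% |
| 0% | 0 | – | no comparison |

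These response rates are assumptions. The table shows precision only and says nothing about bias.

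**4. The behaviour score**

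Let a be the fall in the proportion going to crowded places, and b and c the rises in mask wearing and hand washing.

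- Item 1 scored protectively: change = a + b + c.
- Yes = 1 on every item: change = −a + b + c.

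The two differ by 2a. The raw sum cancels the effect when a = b + c and reverses it when a > b + c. With assumed changes:

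| a, b, c | Protective scoring | Raw sum |
|---|---|---|
| 0.10, 0.10, 0.10 | +0.30 | +0.10 |
| 0.10, 0, 0.10 | +0.20 | 0.00 |
| 0.20, 0, 0.10 | +0.30 | −0.10 |

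For individuals under the raw sum, someone who avoids crowds, wears a mask and washes hands scores 2. Someone who does both protective acts and also goes to crowded places scores 3.

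**The case against.** The strongest reply is that the article does not say what a critical reader might take from it.

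- **Controls and the channel.** A reader might infer that controls are shut out of the survey, or are let into the learning group and receive the intervention. The text supports neither. It places the link on Facebook without saying that it sits inside the closed group, and its wording is permissive. A separate control page, a direct message or the same link sent another way would all fit. The Study 2 data-collection flow chart (Figure 4) is not available here, and a condensed article may leave survey distribution to the full protocol. This stands: unequal access is not established. What remains is that the one route described is tied to the intervention platform.
- **Direction and size of bias.** A reader might infer bias in favour of the intervention. Selective response by engaged users could act that way, but contamination of controls would normally pull towards no difference. One can also construct a figure. If 30% of the intervention arm is lost and those lost score 0.5 SD below completers, the full-arm mean is 0.7m + 0.3(m − 0.5 SD) = m − 0.15 SD, so completers overstate it by 0.15 SD. That compares means within one arm and assumes no similar loss among controls. The planned mixed model can use earlier observations from people who later drop out. The figure is therefore not an estimate of bias in the Time × Group effect and should not be set against d = 0.245.
- **Facebook Insights.** The sentences that follow define self-report items and a Qualtrics survey, so a workable method is present. That makes the Insights sentence easy to correct, but as it stands it names a source that cannot supply the data.
- **Item coding.** No coding is stated, the items are referenced to published sources, and a 0–3 total is compatible with item 1 reversed. Coding is often left to an analysis plan. This stands, so the score is a matter for clarification only.

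**Conclusion.** The point holds in a limited form and should be settled before data collection. Section 8.2.4 names a source for knowledge and behaviours that can measure only engagement. It also places the only stated reporting route on the platform that delivers the intervention, with none stated for controls. Followed as written, this makes response depend on engagement and possibly on arm.

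No size or direction of bias can be given. The primary outcome, eHEAL, is affected only if it is collected through the same link, which the phrase about other outcomes suggests but does not settle. The power figures of 91.6%, 85.2% and 69.8% rest on assumed response rates and ρ = 0.5.

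The behaviour score is a lesser matter and concerns a secondary outcome only. A raw sum of yes answers would shrink the effect whenever crowd-going falls. It would reverse it only if that fall exceeded the other two gains combined. Whether item 1 is left unreversed is neither stated nor ruled out.

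**What to change.** Amend Section 8.2.4 as follows:

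- Send the same Qualtrics link to both arms on the same dates, by personal message, SMS or email outside the learning group. Include people who have left the group.
- Restrict Facebook Insights to engagement in the intervention arm, and name the Qualtrics survey as the source for knowledge and behaviours.
- As a clarification, score item 1 as having avoided crowded places (yes = 1), so that 3 is the most protective total. State one recall window for all three behaviour items, since the past-week window is attached only to mask wearing.

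The cost is a change of wording and survey set-up, collection of contact details in both arms, and individual reminders. The Viber and WhatsApp contacts in Section 8.2.3 belong to the learning programme's small groups, so contact details for controls should be planned for explicitly. The sample size and the planned model do not change.

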### 8.1. Aims

To develop and assess the efficacy of DHL interventions on self-protection of COVID-19 and promoting COVID-19 vaccination among EMs, Chinese PWCI and CGs in HK. *Objective 1.* To co-create DHL interventions with these three groups susceptible to COVID-19 and meet their specific needs in DHL to prevent infection. *Objective 2.* To assess the efficacy of the DHL interventions on eHealth literacy, vaccine literacy and actions taken for COVID-19 prevention.

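### Study 2 tests eHEAL by a non-directional Time × Group interaction over five occasions; one baseline-adjusted post-intervention contrast from the same model would answer the efficacy question more directly and, for a small sustained effect, with more power

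*Protocol article*

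**What the plan says.** The second objective of Study 2 (section 8.1) is: "To assess the efficacy of the DHL interventions on eHealth literacy, vaccine literacy and actions taken for COVID-19 prevention". The primary outcome is eHEAL. On timing, section 8.2.4 says "Five measurements will be made: baseline, after the 8-week intervention (Month 2", with later visits after the boosters at Months 3, 4 and 6.

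Section 8.2.4 then sets out a linear mixed model for each continuous outcome with Time, Group and Time × Group, and gives one statement on how to read it: "A significant result of the interaction term (Time × Group) will indicate a differential change in the outcome variable". It names no single treatment contrast and no primary time point, does not use baseline as a covariate, and does not say whether Time is categorical or continuous.

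The sizing in section 8.2.1 targets the same term. It starts from an earlier study that "reported a small-to-moderate effect size (d = 0.245", takes "with five repeated measurements over a 6-month period, a total sample size of 108 subjects (i.e., 54 per group" as "required to achieve a power of 90% when using a repeated-measures analysis of variance", and aims "to detect a significant between-group interaction effect at 5% significance (G*Power 3.1".

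**The concern.** The question in section 8.1 is whether the intervention improves eHealth literacy. With five occasions and categorical Time, the null hypothesis of the interaction is that the two mean profiles are parallel, on 4 degrees of freedom. That null is rejected by a gain, by a loss, or by a difference at one visit that has gone by the next. A significant result would therefore not by itself show improvement, and the test yields no single effect estimate.

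There is also a cost in power. If the difference appears by Month 2 and persists, the information lies in one direction (post-baseline against baseline), and the omnibus test spreads it over four. The randomised baseline is treated as one more outcome rather than as a covariate, which discards further precision. At stake is the chance of missing a small, lasting benefit in each of the three trials (ethnic minorities, people with chronic illness, caregivers).

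**Working it through.** **Inputs from the protocol article.** d = 0.245, five measurements, 5% significance, 90% power, 108 completers (54 per group), 30% attrition, 156 recruited (section 8.2.1); 1:1 allocation (section 8.2.3); visits at Months 0, 2, 3, 4 and 6 (section 8.2.4).

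**Assumptions, not in the article.** Equal variances; compound symmetry with correlation ρ (0.5 unless stated); d entered in G*Power as f = d/2 = 0.1225; categorical Time.

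**1. Reproducing the sizing.** For the within-between interaction, λ = N·f²·m/(1−ρ) with df 4 and 4(N−2). With N = 108, m = 5 and ρ = 0.5, λ = 108 × 0.1225² × 5/0.5 = 16.2 and power is 91%. With f rounded to 0.12, power is 90%. The stated 108 is therefore reproduced with the 4-df test; f = 0.245 would give N = 28. For attrition, 54/0.7 = 77.1, rounded up to 78 per group, or 156.

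**2. What that effect means as a held difference.** For a group difference δ at all four post-baseline visits and zero at baseline, the squared deviations of the difference profile sum to 0.8δ². So λ = (N/4) × 0.8δ²/(1−ρ) = 0.2Nδ²/(1−ρ). Equating this to 5Nf²/(1−ρ) gives δ = 5f = 0.61 SD. The planned 90% thus corresponds to a held difference of about 0.61 SD. A held difference of 0.245 SD is a much smaller target for this test.

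**3. The alternative contrast.** The mean of the four post-baseline visits, adjusted for baseline, has residual variance (1+3ρ)/4 − ρ². At ρ = 0.5 this is 0.625 − 0.25 = 0.375. The non-centrality is δ/√(4 × 0.375/108), with 105 df. At δ = 0.245 it is 2.08, giving 54% power. The interaction has λ = 0.2 × 108 × 0.245²/0.5 = 2.59, giving 21%. In 20,000 simulated trials the figures were 53.6% and 21.3%, and the interaction's type I error was 5.1%.

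**4. Held difference, N = 108.**

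| ρ | δ (SD) | Interaction | Adjusted average | Loss (points) |
|---|---|---|---|---|
| 0.3 | 0.245 | 16% | 53% | 37 |
| 0.3 | 0.35 | 30% | 83% | 53 |
| 0.3 | 0.61 | 78% | 99.9% | 22 |
| 0.5 | 0.245 | 21% | 54% | 33 |
| 0.5 | 0.35 | 41% | 84% | 42 |
| 0.5 | 0.61 | 91% | 99.9% | 9 |
| 0.7 | 0.245 | 34% | 66% | 32 |
| 0.7 | 0.35 | 65% | 92% | 27 |
| 0.7 | 0.61 | 99% | >99.9% | 1 |

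**5. Where the loss comes from.** At 0.245 SD and ρ = 0.5, a 1-df change contrast without baseline adjustment has 36% power. Of the 33 points, 36 − 21 = 15 come from the 4 df and 54 − 36 = 18 from not adjusting for baseline.

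**6. Other shapes.** If the difference builds linearly by actual month, power is 38% v 56% (0.4 SD at Month 6, ρ = 0.5) and 82% v 85% (0.5 SD, ρ = 0.7). If the single contrast is baseline-adjusted Month 6 alone and the difference is held, it has 31% against 21% at 0.245 SD and 95% against 91% at 0.61 SD (ρ = 0.5).

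**7. Non-specific rejection (N = 108, ρ = 0.5).** A 0.6 SD difference at one post-baseline visit, in either direction, is rejected by the interaction with 90% power and by the averaged contrast with 24%. For a crossing pattern of ±0.4 SD that averages zero, the figures are 99.9% and 5%.

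**The case against.** The strongest reply is that nothing here is an error. The section sets out to examine group differences in change, and the interaction tests that. Sizing and analysis agree, and the type I error is correct. All of this stands: the weakness is the choice of target.

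A second reply is that the article condenses a fuller protocol, where direction, follow-up contrasts and a primary time point would normally sit. It is right that their absence is no finding. But the article does state which test is used and sizes the trial on it, so this is a stated choice that can be discussed.

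Third, the 4-df form is inferred. With linear Time the test would be a signed 1-df slope and would not reject for every non-parallel pattern. The sizing makes the omnibus form the natural reading. The slope would not rescue power for a held difference either: 22% at 0.245 SD, ρ = 0.5.

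Fourth, the held shape is assumed. The article does not say that the boosters serve to maintain a gain, and measuring after each is equally compatible with a building effect, for which the loss is smaller.

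Three stronger readings are tempting and unsupported. One is that the plan forfeits 30 to 40 points of power in general. That holds only for small held differences at certain correlations, and at the effect behind the planned 90% the loss is about 9 points (ρ = 0.5). Another is that the investigators would claim efficacy whatever the direction. The article says only that a significant interaction indicates differential change, and the model also gives signed estimates by visit. The third is that 108 is miscalculated. It reproduces under ordinary assumptions.

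**Conclusion.** The point holds as a cheap improvement and not as an error. The planned interaction is valid and consistent with the sizing. It is, however, non-directional, sensitive to transient and crossing patterns, unadjusted for baseline, and inefficient for a sustained difference. The pattern argument (step 7) rests on the 4-df reading and does not depend on the true effect being small.

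The size of the power loss is conditional. For a difference held over Months 2 to 6 with 54 per group, it runs from about 1 to 53 points over correlations 0.3 to 0.7 and differences of 0.245, 0.35 and 0.61 SD. At 0.245 SD and correlation 0.5 it is 33 points, roughly half of it due to not adjusting for baseline. The article gives neither the correlation nor the expected time pattern, so no single figure should be quoted without its assumptions.

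**What to change.** In section 8.2.4, make the primary eHEAL test one prespecified contrast from the same mixed model: the group difference averaged over Months 2, 3, 4 and 6, with baseline eHEAL as a covariate (or baseline means constrained equal across groups). Report the estimate with its 95% CI and claim efficacy only if it favours the intervention. Keep Time × Group as a secondary description of the time course.

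In section 8.2.1, add a sentence giving the power of this contrast at N = 108 with its assumptions: for example, at correlation 0.5, 54% at a held 0.245 SD, 84% at 0.35 SD and 99.9% at 0.61 SD. State which of these is the intended target.

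The visits, data and sample size do not change. The costs are that the sample-size text, now written for the interaction, must be reworded, and that a difference confined to one visit would be seen only in the secondary analysis.
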